### 3.1. Primary outcome measurements

The SDS (41) and the SAS (42) are two common self-rating depression and anxiety scales, respectively, which can play a significant role in measuring the severity of symptoms of depression and anxiety in adults. These two scales include 20 items, and a four-point system (from 0 to 4) is applied for most items. As a clinical instrument, it has outstanding reliability and validity.

### 3.2. Secondary outcome measurements

The CD-RISC (9) has been shown to be a valid and reliable clinical instrument that can measure individual mental resilience levels. There are 25 items that can be divided into three subscales (i.e., toughness, strength, and optimism). These subscales use a five-point system, with each score ranging from 0 (almost never) to 5 (almost always).

### 3.3. Other psychological scales

The ISI (43) is a five-point Likert-type scale with a 7-item self-report that assesses one’s subjective perception of insomnia over the previous week. With high test–retest reliability and internal consistency, the ISI will be implemented for evaluations in this study.

The PSSS (44) consists of 12 items that are designed to evaluate overall perceived social support. The score of the Chinese version of the PSSS, rated from 1 (very false for me) to 7 (very true for me), will be employed. It consists of three dimensions, namely, family support, friend support, and other support.

The SASE is a self-designed questionnaire with eight questions. The scores of the first seven questions are rated from 1 (strongly disagree) to 4 (strongly agree). Some samples of the questions are as follows: “I can accept psychological intervention in the form of self-help micro-videos.” “The content of the micro-videos and assignments is easy to understand.” “Micro-video psychological intervention is helpful for me.” The last one is an open question about your suggestions and opinions for our psychological intervention.

## 4. Statistical analysis

The analyses will be conducted based on the principle of intention-to-treat, meaning that all participants who have been randomized will be included in the analyses. In statistical tests, the SPSS version 23.0 software will be selected and used. The relevant data will be considered statistically significant if P < 0.05. The categorical variables are statistically described by the number of cases (percentage), and the chi-square analysis is used for intergroup comparison. Continuous variables are statistically described using mean ± standard deviation (M ± SD), and the independent sample *t*-test is used to make comparisons between the two groups. Also, repeated measures, such as ANOVA, are used to compare the degree of symptom improvement between the intervention group and the control group, and the interaction of group × time is analyzed. Missing data will be imputed using the estimation maximization (EM) method in SPSS version 23.0.

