### 2.7. Sample size

The results of the pre-experiment were used as a reference for the estimation of the sample size. The preliminary results of the intervention group before and after the intervention in the pre-experiment are shown in Table 1.

From previous studies (39), we know that there was no significant statistical difference between the result of the waiting list control group’s score before and after. Thus, we used the score before the intervention as the outcome score of the waiting list control group and the score after the intervention as the outcome score of the intervention group to calculate the sample size that was based on the two-sample mean to improve the efficiency of the experimental design (40) in the calculation formula when computing the sample size.

(1)
$$\eta_{A}=\kappa \eta_{B}\text{⁢and⁢}\eta_{B}=(1+\frac{1}{k}\,){\left(\sigma \frac{z_{1-\alpha }+z_{1-\beta }}{\mu_{A}-\mu_{B}-\delta }\right)}^{2}$$

κ represents the ratio of two groups of sample size. In this study, κ = *1*. σ stands for standard deviation. In this study, the standard deviation before intervention was considered the population standard deviation. *Z1*-α represents the value of the standard normal distribution function corresponding to the level of class I error (test level). *Z1*-β represents the value of the standard normal distribution function corresponding to the level of class II error (test level); Delta represents the boundary between the two sets of values.

The test level α = 0.05 and the degree of certainty β = 0.20 were set. The combined standard deviation of SDS and SAS as well as the boundary values of different outcome indices (the difference between indices considered to be meaningful professionally) were used to calculate the sample size, as the results are shown in Table 2. In light of feasibility, funding, and other practical factors, the study selected 100 cases in each group, or 200 cases in total, as the sample size.

**TABLE 2 T2:** Minimum sample size of each group required to find differences between groups at different threshold levels.

Outcome indicators	Outcome score of intervention group	Outcome score of control group	Combined standard deviation σ	Boundary value δ	Sample size	Loss rate 30%
SDS	50	61	8	5	22	33
				6	32	43
				7	50	61
				8	88	98
				9	198	209
SAS	42	51	7	4	25	36
				5	38	49
				6	68	79
				7	152	163

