## 3. Outcome measurements and instruments

The study assessment will be completed online by the subjects on a self-help basis. Self-rating scales were used in this study. The analysis of these scales will be conducted by a statistician without knowing how the subjects are allocated.

The efficacy indicators include (1) the primary outcome: the change in the SDS score and the SAS score between groups at different times. In particular, if the reduction rate is ≥50%, an obvious effect will be shown; if the rate is <50 and ≥25%, the effect is only average; and if the rate is <25%, no clinical effect will exist. (2) The secondary efficacy outcome is based on The Connor-Davidson Resilience Scale (CD-RISC) score, which can be increased as symptoms of anxiety and depression improve during the treatment process. In addition, measurements including the Insomnia Severity Index (ISI) and the Perceived Social Support Scale (PSSS) will be provided.

The applicability indicators include the intervention completion rate, the dropping rate, and the Self-Assessment Scale of the Overall Efficacy and Satisfaction of Participants (SASE) score.

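### By default the ordered SDS and SAS response classes would get an unordered chi-square test with a nearly empty top class; a trend test is a free, minor improvement

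*Protocol article*

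**What the plan says.** Section 3 (Outcome measurements and instruments) sets "the primary outcome: the change in the SDS score and the SAS score between groups at different times". It then grades the reduction rate: "if the reduction rate is ≥50%, an obvious effect will be shown; if the rate is <50 and ≥25%, the effect is only average", and anything under 25% counts as no clinical effect. These are three classes with a clear order from better to worse.

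Section 4 (Statistical analysis) has one rule for categorical data: "The categorical variables are statistically described by the number of cases (percentage), and the chi-square analysis is used for intergroup comparison". It names no ordinal or exact method and does not mention the response classes. The scores have their own analysis. Continuous variables are compared by t-test, and repeated-measures methods with a group × time term "are used to compare the degree of symptom improvement between the intervention group and the control group". The significance rule is "The relevant data will be considered statistically significant if P < 0.05".

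Section 2.7 (Sample size) fixes 100 per arm. Table 1 gives the pilot means and SDs (N = 24).

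**The concern.** A Pearson chi-square test on a table of three classes by two arms has 2 degrees of freedom. It would give the same result if the class labels were shuffled, so part of the test is spent on patterns that are not better-versus-worse. It also relies on adequate expected counts. A 50% fall from the pilot SDS baseline is about 31 points, while the pilot mean fall was 11.78, so the top class should be very sparse. These classes are what the plan uses to call an effect clinically obvious, average or absent. A less sensitive comparison of them could blur that statement. It would also leave the choice of test, or of merging classes, until after the sparse table has been seen.

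**Working it through.** **The plan's own figures.** The article gives no figure for the response classes. Table 2 concerns mean scores and reproduces from formula (1). For SDS with boundary 5: 2 × [8 × (1.645 + 0.842)/(61 − 50 − 5)]² = 22, as printed.

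**Inputs from the documents.** 100 per arm. Pilot SDS 61.41 (SD 4.92) before and 49.63 (SD 10.11) after, a fall of 11.78. Pilot SAS 50.89 (SD 7.05) before and 42.40 (SD 5.86) after, a fall of 8.49.

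**Assumptions (not in the documents).** Pre/post correlation 0.4. Wait-list mean fall 3 points. Baseline and fall normal, and independent when classes are formed.

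**Step 1: SD of change** = √(SD₁² + SD₂² − 2r·SD₁·SD₂).
- SDS: √(24.21 + 102.21 − 39.79) = 9.3
- SAS: √(49.70 + 34.34 − 33.05) = 7.14

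**Step 2: class probabilities.** P(fall ≥ c × baseline) = 1 − Φ[(c·b − m)/√(s² + c²·s_b²)], where b and s_b are the baseline mean and SD, and m and s the mean and SD of the fall.
- SDS, ≥50%, intervention: (30.705 − 11.78)/√(86.49 + 6.05) = 1.967, so 2.5%
- SDS, ≥50%, control: (30.705 − 3)/9.620 = 2.880, so 0.2%
- SDS, ≥25%, intervention: (15.35 − 11.78)/9.381 = 0.381, so 35.2%; control: (15.35 − 3)/9.381 = 1.317, so 9.4%
- SAS, ≥50%, intervention: (25.445 − 8.49)/√(50.98 + 12.43) = 2.129, so 1.7%; control: (25.445 − 3)/7.963 = 2.819, so 0.2%

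The expected count per arm in the top class is (2.5 + 0.2)/2 = 1.3 for SDS and (1.7 + 0.2)/2 = 0.95 for SAS. Two of six cells (33%) are below 5, against the usual limit of 20%.

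A second model has bivariate-normal pre and post scores, correlations from 0 to 0.7 and an unchanged control mean. It gives 1.3 to 3.4 per 100 in the intervention arm and 0 to 0.2 in controls for SDS, and 0 to 0.7 and 0 to 0.1 for SAS. The class is nearly empty under either model.

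**Step 3: error rate with no true difference.** Simulated at nominal 5%, the Pearson test rejects in about 3.6 to 4.6% of trials under the first model. Under the second it rejects in 3.3 to 3.8% for SDS and 4.0 to 5.2% for SAS. The trend test stays near 5%.

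**Step 4: power, 100 per arm, wait-list fall 3 (simulation).** The last column is the two-sided t-test on score change: Φ[d/(s√(2/100)) − 1.97]. For SDS, d = 4: Φ(3.04 − 1.97) = 86%.

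| Scale | True difference | Pearson | Trend | Loss (points) | t-test on change |
|---|---|---|---|---|---|
| SDS | 4 | 41% | 48% | 7 | 86% |
| SDS | 5 | 59% | 68% | 9 | 97% |
| SDS | 6 | 78% | 85% | 7 | 99% |
| SDS | 8.78 (11.78 − 3) | 99.1% | 99.7% | under 1 | >99% |
| SAS | 4 | 61% | 70% | 9 | 98% |
| SAS | 5.49 (8.49 − 3) | 90% | 94% | 4 | >99% |

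Repeat runs agree to within about 2 points.

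**Step 5: sensitivity.** In the second model, at the pilot effect with unchanged controls, the loss is under 1 point for both scales, and at most about 2 points with 70 per arm. At assumed SDS differences of 3, 4 and 5 with SD 10.11, Pearson gives 29–34%, 50–55% and 69–75%, against 39–44%, 61–66% and 79–84% for the trend test. That is a loss of about 9 to 12 points.

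**The case against.** The strongest reply is that the article never says the response classes will be tested between arms. Section 3 uses them to label the size of a score change, and the chi-square sentence in section 4 is general. Moving to ordinal or exact methods for sparse tables is routine detail for an analysis plan that is not shown. This stands in part: the use of chi-square on the classes is an inference from the only test named for categorical variables. The point therefore has to be conditional. It rests on a stated method that suits these classes poorly, not on an omission.

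A second reply is that the loss is selective, since at the pilot effect it almost vanishes for SDS. That is correct. Smaller differences still deserve attention. The pilot effect is an uncontrolled change in 24 people. The Discussion expects some spontaneous recovery and self-help among controls. The boundary values that Table 2 treats as professionally meaningful start at 5 for SDS and 4 for SAS.

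A reader might go further and infer that the chi-square test is invalid here, or that a real benefit would go undetected. Neither is supported. The expected-count rule fails, but the error rate stays at or slightly below nominal. The planned t-test on scores has 86% power or more at the very differences where the class comparison is weak.

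**Conclusion.** The point holds as a minor one. If the classes are compared between arms by the only categorical test the article names, their order is discarded and the ≥50% column is nearly empty. The cost is a slightly conservative test and about 7 to 9 points of power at modest differences (SDS 4 to 6, SAS 4). At the pilot fall less 3 it is under 1 point for SDS and about 4 for SAS. These figures rest on the assumed correlation of 0.4, the 3-point wait-list fall and normal scores; the second model puts the loss at about 9 to 12 points for SDS differences of 3 to 5. The trial's main conclusion does not depend on this comparison, because symptom improvement is judged on the continuous scores.

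**What to change.** Add one sentence to section 4: if the ordered SDS and SAS response classes are compared between arms, a linear-by-linear (trend) test or a Mann-Whitney test is used, with exact P values where expected counts are below 5; the Pearson chi-square test is kept for unordered categorical variables. One of the two ordinal tests should be named in advance.

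The change needs no new data and no change to the sample size. The trend statistic comes from the same cross-tabulation. Fixing it before analysis also removes a choice of test, or of merged classes, made after the sparse table is seen.

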**Methods:**

In this parallel-group, randomized controlled trial, a total of 200 mild to moderately depressed and/or anxious adults seeking self-help will be randomly recruited and assigned to either the micro-video psychological intervention group or the wait list control group. Online measurements by self-assessment will be taken at baseline, post-intervention, 1-month, and 3-month follow-up.

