### 2.4. Randomization

Randomization of the trial will be based on a computer-generated randomization list. After returning their ICF and completing the baseline questionnaire, people who meet the inclusion criteria will be randomly allocated to the *MVPTC* intervention group or to the waiting list control group and then will receive a notification *via* WeChat message. Later, a computer program will allocate participants using a generated randomization list. Block randomization in blocks of two will be used to ensure an equal distribution of participants across conditions.

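### Neither the t-test nor the group × time ANOVA adjusts for the baseline SDS or SAS score, which costs efficiency (not validity) and does not directly estimate the difference the objective asks for

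*Protocol article*

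**What the plan says.** The primary outcome (section 3) is "the change in the SDS score and the SAS score between groups at different times". No single visit is named as primary. The abstract gives four assessments: "Online measurements by self-assessment will be taken at baseline, post-intervention, 1-month, and 3-month follow-up".

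Section 4 names two methods for continuous outcomes. For continuous variables in general, "the independent sample *t*-test is used to make comparisons between the two groups". For symptoms, "repeated measures, such as ANOVA, are used to compare the degree of symptom improvement between the intervention group and the control group". The only term that this second method is said to examine comes next: "the interaction of group × time is analyzed". No covariate appears in that section or elsewhere in the article.

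The baseline scores are available in time. Section 2.4 places allocation "After returning their ICF and completing the baseline questionnaire", and section 2.3 uses SDS and SAS as entry criteria.

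The sample size in section 2.7 also rests on an unadjusted comparison of two means. It states that "The test level α = 0.05 and the degree of certainty β = 0.20 were set".

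**The concern.** Each primary outcome has its own baseline score, measured before allocation and likely to predict the later score. A t-test on the follow-up score ignores it. A t-test on change uses it with a fixed slope of 1, which is efficient only if the true slope is near 1. Neither estimates the slope from the data.

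The ANOVA raises a second issue. If baseline is one of its time levels, the treatment effect sits in the group × time interaction, which has (2 − 1)(4 − 1) = 3 degrees of freedom. That test asks whether the two profiles differ in any way. Section 1.2 asks whether symptoms are reduced compared with the wait list, which is a directional question about a mean difference.

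At stake are the width of the confidence interval, and power if the true effect is much smaller than in the pilot. That is plausible. The planning difference is an uncontrolled before-after change, and section 5 concedes that mild to moderate symptoms may resolve on their own and that controls may use self-help.

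**Working it through.** **Inputs.** Planning means are 50 v 61 (SDS, SD 8) and 42 v 51 (SAS, SD 7), with 100 per group (section 2.7, Table 2). Pilot SDs before and after are 4.92 and 10.11 (SDS) and 7.05 and 5.86 (SAS), from 24 participants (Table 1). The baseline-outcome correlation r is not given, so 0.3 to 0.7 is assumed.

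**The plan's own figure.** n per group = 2[σ(z₁₋α + z₁₋β)/(difference − δ)]², with z₁₋α = 1.645 and z₁₋β = 0.842. For SDS with δ = 8: 2 × (8 × 2.487/3)² ≈ 88, as in Table 2. All nine sizes reproduce in this way. The formula contains no r, so the planning is unadjusted.

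**Variances.** With s₀ and s₁ the SDs before and after:
- post score: s₁²
- change: s₀² + s₁² − 2r·s₀·s₁, which is 2(1 − r)s² with equal SDs
- ANCOVA: s₁²(1 − r²)

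Pilot SAS at r = 0.5:
- post: 5.86² = 34.3
- change: 49.70 + 34.34 − 41.31 = 42.7
- ANCOVA: 0.75 × 34.34 = 25.8

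Pilot SDS at r = 0.5:
- post: 10.11² = 102.2
- change: 24.21 + 102.21 − 49.74 = 76.7
- ANCOVA: 0.75 × 102.21 = 76.7

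The two SDS figures agree because the implied slope, 0.5 × 10.11/4.92 = 1.03, is almost exactly 1. For SAS it is 0.5 × 5.86/7.05 = 0.42.

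| r | ANCOVA / post | ANCOVA / change, equal SDs | SAS pilot: change / post | SAS saving of ANCOVA v change | SDS pilot: change / post | SDS saving of ANCOVA v change |
|---|---|---|---|---|---|---|
| 0.3 | 0.91 | 0.65 | 1.73 | 47% | 0.945 | 4% |
| 0.5 | 0.75 | 0.75 | 1.24 | 40% | 0.75 | 0% |
| 0.7 | 0.51 | 0.85 | 0.76 | 33% | 0.556 | 8% |

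By the first ratio, about 91, 75 or 51 per group with ANCOVA match 100 per group with a post-score t-test.

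**Power.** Illustration: difference 3, SD 8 at every visit, 100 per group, two-sided 0.05. The 3 is 61 − 50 − 8, the net difference in the SDS row with the largest boundary that 100 per group covers. The interaction test assumes equal correlations between visits. Its non-centrality is n/[2σ²(1 − r)] times the sum of squared deviations of the visit effects from their mean.

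At r = 0.5:
- post-score t-test: √(100 × 9/128) = 2.65, power 75.5%
- ANCOVA at a visit where the difference is 3: √(100 × 9/(128 × 0.75)) = 3.06, power 86.5%
- interaction, effects 0, 3, 3, 3: (100/64) × 6.75 = 10.5, power 78.5%
- interaction, effects 0, 3, 2, 1: (100/64) × 5 = 7.8, power 64.3%

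| r | Post t-test | Change t-test | 3-df, constant effect | 3-df, fading 3, 2, 1 | ANCOVA |
|---|---|---|---|---|---|
| 0.3 | 75.5% | 61.1% | 62.5% | 48.6% | 79.4% |
| 0.5 | 75.5% | 75.5% | 78.5% | 64.3% | 86.5% |
| 0.7 | 75.5% | 92.8% | 95.5% | 87.1% | 96.0% |

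With 70 per group and r = 0.5, the t-test has 60.2%, the interaction 61.5% (constant) or 47.8% (fading), and ANCOVA 72.6%. At the planning differences of 11 on SDS (SD 8) and 9 on SAS (SD 7), an unadjusted test with 70 per group already exceeds 99.9%.

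**The case against.** The strongest reply is that nothing here is wrong: randomisation makes the unadjusted tests valid, power is ample at the pilot effect, and covariates, visit contrasts and intervals are often left to an analysis plan that is not shown. The first two parts stand and limit the weight of the point. The third stands only in part. The article does not leave the methods open; it names them, and the point is about the methods named.

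Four stronger readings are tempting and should not be drawn.
- A reader might infer that the treatment estimate is biased. It is not. A chance baseline imbalance widens the error of an unadjusted estimate but does not bias it under randomisation.
- A reader might infer that baseline information is wholly discarded. The t-test sentence is generic and is not tied to SDS or SAS. If baseline is an ANOVA level, the interaction compares changes from baseline and so uses it in part. That baseline is a level is the natural reading of a change outcome and four assessments, but it is not stated.
- A reader might infer that including baseline dilutes a group main effect. Section 4 plans no test of one.
- A reader might infer a fixed fall from 80% to about 64% power for three degrees of freedom against one. That holds non-centrality constant and credits the extra visits with no information. For a constant effect at r = 0.7 the interaction test is within half a point of ANCOVA.

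The SDS result is also a fair objection: with the pilot SDs, ANCOVA gains almost nothing over a change score on that scale.

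**Conclusion.** The point holds as one of efficiency and interpretability. The named methods do not adjust for a baseline score already in hand, and the omnibus interaction does not directly supply the directional difference in section 1.2. The gain is clear against a post-score t-test on either scale and against a change score on SAS. It is small against a change score on SDS.

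The size rests on three assumptions. First, r lies between 0.3 and 0.7; the entry ranges in section 2.3 may lower it, though a participant who enters on one scale need not reach the lower limit of the other. Second, the pilot SDs, which come from 24 treated participants, apply to both arms. Third, the visits are equally correlated, for the interaction figures. The power gain matters only if the true difference is well below the pilot's. The change is worth making because it needs no new data, but the trial does not fail without it.

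**What to change.** In section 4, analyse each of SDS and SAS with its baseline score as a covariate. Use ANCOVA, or a mixed model on the three post-baseline visits with baseline and baseline × visit as terms. Report the adjusted mean difference with its 95% CI at each visit. Keep the t-test and the group × time ANOVA as supportive.

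The cost is small but not nil.
- Section 3 must name one primary visit, and the choice matters. In the fading illustration, ANCOVA at a visit where the difference is only 1 has √(100/(128 × 0.75)) = 1.02, so about 17% power at r = 0.5.
- A mixed model must be reconciled with the EM imputation in section 4 and with the statement there that all randomised participants are analysed. It uses observed visits without imputation, and a participant with no post-baseline score contributes nothing to it. The text should say which approach is primary and how such participants are handled.

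No extra participants or assessments are needed.

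### Single EM imputation analysed as observed data understates standard errors if arm is in the imputation model, or shrinks the effect if it is not

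*Protocol article*

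**What the plan says.** Everything that matters here is in section 4 (Statistical analysis) of the protocol article.

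- Analysis set, under intention-to-treat: "all participants who have been randomized will be included in the analyses".
- Tests: "the independent sample *t*-test is used to make comparisons between the two groups"; in addition "repeated measures, such as ANOVA, are used to compare the degree of symptom improvement between the intervention group and the control group".
- Differential change over the visits is covered by a further statement: "the interaction of group × time is analyzed".
- Threshold: "The relevant data will be considered statistically significant if P < 0.05".
- Missing data: "Missing data will be imputed using the estimation maximization (EM) method in SPSS version 23.0".

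The section names no multiple imputation, no variance correction, no likelihood-based model and no sensitivity analysis, and it does not say whether arm enters the EM model.

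Two other places bear on how much data may be missing. Table 2 in section 2.7 has a column headed with a 30% loss rate, the only loss figure in the document. Section 5 expects dropouts in either arm and plans a dropout analysis and a survey of reasons.

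**The concern.** Taken together, these statements produce one completed data set of 100 per arm, which is then analysed as if every score had been recorded. That causes one of two problems.

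- **Arm in the EM model.** Each gap receives a value predicted from the participant's own arm. The estimate is unbiased under random loss. But the predicted values have too little spread and are counted as full observations, so the standard error is too small.
- **Arm not in the EM model.** Missing scores in both arms are predicted from pooled data, which pulls the arms together. The null hypothesis is still tested at about the right level, but a real effect is understated and its confidence interval is centred in the wrong place.

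SDS and SAS are the primary outcomes, so the P-values and intervals for the main result are affected in either case.

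**Working it through.** **Table 2 first.** Its inputs are in section 2.7: "The test level α = 0.05 and the degree of certainty β = 0.20 were set", SDS 50 against 61 with SD 8, SAS 42 against 51 with SD 7. The formula is n = 2 × [σ(z₁₋α + z₁₋β) / (difference − boundary)]², with z₁₋α + z₁₋β = 1.645 + 0.842. For SDS at boundary 5, n = 2 × (8 × 2.487 / 6)² = 21.98, so 22. All nine sizes before loss reproduce: SDS 22, 32, 50, 88, 198; SAS 25, 38, 68, 152.

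The loss column does not behave as a 30% inflation. For SDS, n / 0.7 gives 32, 46, 72, 126, 283, against the stated 33, 43, 61, 98, 209. For SAS it gives 36, 55, 98, 218, against 36, 49, 79, 163. The column is n plus 10 or 11 throughout. I therefore treat 30% as one point in a range.

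**Assumptions.** 100 per arm is from the plan, and SD 8 is the SDS value in Table 2. The document gives no between-visit correlation (ρ), so 0.3–0.7 is assumed. Loss is assumed completely at random with fraction L, and tests are two-sided at 0.05.

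**Arm in the EM model, t-test at 3 months, all loss after baseline.** In closed form:

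- True SE = √{2σ²[(1 − ρ²)/(100(1 − L)) + ρ²/100]}
- Reported SE = √{2σ²[(1 − L) + Lρ²]/100}
- Type I error ≈ 2 × [1 − Φ(1.96 × reported / true)]

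With σ = 8, ρ = 0.5, L = 0.30:

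- True SE = √{128 × [0.75/70 + 0.25/100]} = 1.30
- Reported SE = √{128 × 0.775/100} = 1.00
- Ratio 0.766, type I error about 13%

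| Loss | ρ | True SE | Reported SE | Type I error |
|---|---|---|---|---|
| 10% | 0.5 | 1.18 | 1.09 | 7.0% |
| 10% | 0.7 | 1.16 | 1.10 | 6.3% |
| 20% | 0.5 | 1.23 | 1.04 | 9.7% |
| 20% | 0.7 | 1.20 | 1.07 | 8.0% |
| 30% | 0.5 | 1.30 | 1.00 | 13.3% |
| 30% | 0.7 | 1.25 | 1.04 | 10.2% |

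Simulation agrees. With 3,000 trials per setting, 30% loss and ρ = 0.5, the mean reported SE was 0.99 against a true SD of 1.29, and type I error was 12.3%. Separate simulations with early and staggered loss and SDs of 8 and 10 span 6–8% at 10% loss, 7–11% at 20% and 8–16% at 30%. The 16% comes from a run with follow-up SD 10 and all loss early. Further results:

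- The group × time ANOVA (Greenhouse-Geisser corrected) rejected a true null in 15–27% of trials at 30% loss (ρ 0.3–0.7), and in 8.6% at 10% loss (ρ = 0.5, early loss).
- Coverage of the 95% interval for the 3-month difference was 85–91% at 30% loss.
- Adding a random residual to the single fill-in (ρ = 0.5, early loss, 30%) still gave 10.5% for the t-test and 18.5% for group × time.
- For comparison, complete cases (70 per arm) had SE 8 × √(2/70) = 1.35 and type I error of about 5%.

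**Arm not in the EM model, 30% loss.** If all loss follows baseline, the arms have the same expected baseline, so imputed scores have the same expected value in both arms. Only the 70% observed carry the effect: 0.70 × 11 = 7.7 and 0.70 × 5 = 3.5. Simulation gave 7.7 for a true 11 and about 3.4–3.6 for a true 5, a loss of about 30%. With staggered loss, later dropouts keep some post-baseline scores that carry the effect. A true 11 was then estimated as 9.0–9.4 (15–18% shrinkage) and a true 5 as 4.1–4.2; a further check gave about 19%. For a true 11 and equal loss in both arms, interval coverage was 12–14% (early) and 50–67% (staggered). Type I error stayed near 5%.

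**The case against.** **The size depends on a loss rate that the plan hardly commits to.** The 30% is a column heading, the column is not computed from it, and "the study selected 100 cases in each group, or 200 cases in total, as the sample size" follows a statement that feasibility and funding decided the number. This stands. A reader might take 30% loss, and the error rates that go with it, as what the trial will see. The document does not support that. At 10% loss the t-test runs at only 6–8%.

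**The two harms exclude each other.** A reader might infer that the trial faces both inflated false positives and a shrunken effect. It does not: with arm in the model the estimate is unbiased, and with arm left out the false positive rate is near nominal. The list of imputation variables is also something an article may leave to the full plan, so the shrinkage is a possibility, not a stated feature of the plan.

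**The worst figures come from the worst pattern.** The 30% shrinkage needs every dropout to leave straight after baseline. The t-test figures refer to 3 months, where cumulative loss is greatest. Under gradual loss the post-intervention comparison suffers less.

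**Perhaps this is detail for the analysis plan.** This does not stand. The article itself names the fill-in method, the tests run on the result and the threshold. The dropout analysis and survey in section 5 describe the loss but correct neither the standard error nor the estimate.

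**Conclusion.** The point holds in conditional form. As written, section 4 analyses singly imputed data as though observed, and neither answer on whether arm enters the EM model makes that valid.

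The standard-error branch follows from the printed plan if arm is in the EM model, and its size grows with loss, from slight at 10% to about two to three times the nominal 5% for the 3-month t-test at 30%. Group × time, the plan's test of differential improvement, fares worse. The shrinkage branch applies only if arm is left out.

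These sizes rest on an assumed correlation, loss completely at random and early or staggered loss patterns. Informative dropout could add bias in either branch and is not quantified here.

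**What to change.** Replace the single EM fill-in for SDS and SAS with one of these:

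1. A likelihood-based repeated-measures mixed model on all observed scores, with arm, visit and arm × visit, an unstructured covariance, and baseline kept as one of the response visits. Section 2.4 places the baseline questionnaire before allocation, so every randomised participant contributes at least one score and the all-randomised rule in section 4 is kept. A model with baseline only as a covariate would drop anyone without a post-baseline score and so conflict with that rule.
2. Multiple imputation with arm and all visits in the imputation model, and variances combined across imputations.

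With either, add a sensitivity analysis for data not missing at random, for example by shifting the imputed scores of intervention participants. The dropout survey already planned can inform the shifts.

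The cost is analysis wording and syntax, and confidence intervals that are wider but correct. Recruitment, assessments and participant burden do not change. Whether the named software version covers each step should be confirmed, because the document does not show it.
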